#### Mediation Analyses (Hypothesis 3 and Exploratory Examination)

These analyses will be based on the criteria of Zhang et al [66] for mediation in multilevel models. A 2-1-1 mediation model (Figure 2) in which the predictor (TP quality) is a level-2 antecedent variable (between-subjects variable) will be used. The potential mediator (program completion rate) and outcomes (child behaviors and parenting variables) are both level-1 variables (ie, repeated measurements-within-subjects variables). This model tests whether the study manipulation of predictor values influences the values of a level-1 mediator, which then affects a level-1 outcome. Mediation analyses will be conducted using relevant codes for Mplus (Muthén and Muthén) [67,68].

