### This Study

This study aims to (1) conduct a fully powered RCT design that can provide strong support for the hypotheses; (2) examine the long-term impact of the treatment and the maintenance of treatment gains over a follow-up period, knowledge that is of great importance when aiming to determine whether enhanced mechanisms of action embedded in unguided interventions are maintained over time (or even better in comparison with standard programs); and (3) examine meditational pathways including whether adherence to the program, measured by module completion rates, mediate reported changes.

The study design is a 2-arm parallel-group RCT with repeated measures. It consists of 2 intervention arms for parents of children with behavior problems. We will follow a large sample of families with parents who report having a child with behavior problems, before, during, and after receiving the DPT they are randomly allocated. In particular, this study has the following hypotheses:

Adherence and usage: Compared with parents who receive DPT-STD, parents who receive DPT-TP will show better adherence to the digital program (operationally defined as program completion rate) and higher metrics of program usage (number of logins, unique days of use, and total time of use).Efficacy: Compared with parents who receive DPT-STD, parents who receive DPT-TP will report greater improvements in child behavior problems (Eyberg Child Behavior Inventory [ECBI] Intensity), parenting practices (Specific Parenting Practices [SPP], The Parenting Scale [PS], and Alabama Parenting Questionnaire [APQ]) and Parental self-efficacy (The Parenting Tasks Checklist; Me as a Parent [MaaP]), as measured pre-post and pre-follow-up.Mediational pathway: Program completion rate will mediate the impact of therapeutic persuasiveness quality on outcome variables.

In addition, we will explore whether the relationship between program usage and changes in parenting variables and child behavior problems is moderated by program quality (moderated mediation).

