### Measures

The study instruments include self-reported questionnaires that will be assessed at all time points for this study (T1-T5) and data on program usage. Parents will also complete a demographic questionnaire at baseline (T1). Participants will be assessed at 3.3 weeks (T2), 6.6 weeks (T3), and 10 weeks (postintervention; T4), and will complete follow-up assessments at 6 months after the beginning of the intervention (follow-up; T5). The self-report measures will be administered through Qualtrics (Silver Lake).

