#### Program Completion Rate and Usage

Program usage (eg, login activities, time spent using the program, modules begun and completed) will be automatically documented within the digital platform. Program completion rate is defined as the number of modules the user completes divided by the number of modules the user is expected to complete (7 in DPT-STD and 4-7 in DPT-TP).

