##### Adaptation to User State

At the end of the first module (introduction), parents will be asked to report about the current state at home, and this will be used to recommend whether to complete the 3 learning modules that are not deemed obligatory: positive interactions, emotion regulation, and effective routines. Parents’ reports on their activities are used to acknowledge their success and to suggest additional actions based on the specific goals reported by parents. Effort related to desired therapeutic activities is adapted based on graded tasks (defined as “load reduction of therapeutic activities” in our therapeutic persuasiveness model [13]). For example, when parents learn how to overcome disobedience (module 6), they will be guided to choose 1 specific behavior problem they would like to focus on first, and then, based on their progress, they will be directed to take additional steps.

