#### Hypotheses 1-2 Analytic Plan

Hypothesis 1 will be examined using a series of 1-way ANOVAs. Specifically, treatment type will be the independent variable (DPT-STD vs DPT-TP) in all analyses, and program completion rate, number of logins, unique days of use, and total time of use will be the dependent variables. If the treatment conditions significantly differ on important demographic or clinical variables, those variables will be added as covariates to the analysis, creating an analysis of covariance (ANCOVA).

Hypothesis 2 will be examined using two 2-way ANOVAs with treatment type (DPT-STD vs DPT-TP), measurement (pre vs post in the first ANOVA and pre vs follow-up in the second), and their interaction as independent variables. Child behavior problems (ECBI Intensity), parenting practices (SPP, PS scales, and APQ), and parental self-efficacy (PTC and MaaP) will be the dependent variables.

Assumptions of ANOVA will be examined for all analyses and corrected if not met using common procedures. For instance, the assumption of equality of variance will be examined using the Levene test, and if not met, we will use weighted least squares or robust tests such as Welch and Brown-Forsythe.

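### The Hypothesis 3 model reads the completion-to-outcome path causally although completion is not randomised, so stable parent characteristics can bias the indirect effect and a lag or time term does not remove this

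*Protocol article*

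**What the plan says.** Mediation is one of the three aims. The hypotheses (This Study) state: "Program completion rate will mediate the impact of therapeutic persuasiveness quality on outcome variables".

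The Mediation Analyses section sets out a 2-1-1 model. Arm is the between-parent (level-2) predictor. Of the rest it says: "The potential mediator (program completion rate) and outcomes (child behaviors and parenting variables) are both level-1 variables". The purpose of the model is given as: "This model tests whether the study manipulation of predictor values influences the values of a level-1 mediator, which then affects a level-1 outcome". No other variable is named.

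The mediator is defined under Program Completion Rate and Usage as "the number of modules the user completes divided by the number of modules the user is expected to complete". The Recruitment Procedure randomises arm 1:1 and nothing else.

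The only covariate rule in the Analytic Plan is in the Hypothesis 1 paragraph of the Hypotheses 1-2 Analytic Plan: "If the treatment conditions significantly differ on important demographic or clinical variables, those variables will be added as covariates to the analysis". Power Estimation assumes a large arm effect on completion (A path) and describes the completion-to-change link (B path) as a small-to-moderate correlation. It mentions no adjustment.

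**The concern.** Randomisation protects the effect of arm on completion and the total effect of arm on outcome. It does not protect the path from completion to outcome, because parents decide how much to complete. Confidence as a parent or existing parenting skill, for example, could plausibly favour both finishing modules and improving.

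Arm is constant within a parent, so an arm-driven mediated effect has to rest on differences between parents, and that is where stable traits confound. Measuring completion before outcome deals with reverse causation, and a time term deals with a shared trend. Neither touches a fixed difference between parents.

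The covariate rule quoted above would not help even if it were carried over to Hypothesis 3. It is triggered by imbalance between arms, whereas the problem is imbalance between parents who complete more and parents who complete less.

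At stake is the explanatory claim of the trial: it could report that therapeutic persuasiveness works through completion when completion contributes nothing.

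**Working it through.** **1. The plan's own figure.** With 80 per arm, d = 0.43 and one-tailed α = .05, power is Φ(0.43 × √40 − 1.645) = Φ(1.075) = 0.859, or 0.856 with the noncentral t. The stated 0.85 reproduces and is not in dispute.

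**2. Inputs.**
- n = 160 and direct arm effect 0.43 SD (Power Estimation).
- A path a = 0.9 SD. The plan says only that it is large. Pilot completion was 31/45 against 12/43, an odds ratio of (31/14)/(12/31) = 5.72, and ln(5.72) × √3/π = 0.96. The smallest pilot usage effect was d = 0.91 (Pilot Study).
- True completion effect: zero.
- One pre-existing trait with correlation r, within arm, with both completion and improvement. **The value of r is an assumption**; the article gives none, so a range is shown.

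**3. Algebra.** With no true completion effect, the spurious B path is b = r × r and the spurious indirect effect is a × b. The A path is almost always significant (z ≈ 0.9 × √40 = 5.7), so false mediation is declared about as often as b is significant. At r = .4, b = 0.16, its standard error is about √((1 − 0.16²)/157) = 0.079, and z ≈ 2.0, which exceeds 1.96 about half the time.

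| r (assumed) | spurious b | spurious indirect effect, SD | share of 0.43 |
|---|---|---|---|
| .2 | 0.04 | 0.04 | 8% |
| .3 | 0.09 | 0.08 | 19% |
| .4 | 0.16 | 0.14 | 33% |
| .5 | 0.25 | 0.23 | 52% |

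**4. Simulation.** 2,000 trials per cell. Mediation is declared when both paths have two-sided p < .05 and the indirect effect is positive, so the nominal rate is about 2.5%.

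| Model | r = 0 | .2 | .3 | .4 | .5 |
|---|---|---|---|---|---|
| Change score on arm and completion | 3% | 7% | 19% | 51% | 89% |
| Between-parent path of the repeated measures | 3% | 7% | 20% | 55% | 91% |
| Lagged completion plus time | 6% | 12% | 26% | 57% | 89% |
| Change score, adding a baseline proxy of reliability 0.5 | 3% | 5% | 8% | 21% | 43% |
| Change score, adding the trait itself | 3% | 3% | 3% | 2% | 3% |

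The lagged model with a time term rises with r much as the first two do. A random-intercept model with a time term gives 10%, 22%, 42%, 77% and 97%, but its 10% at r = 0 comes from parent-specific slopes that it omits, so the first two rows are the clean comparison.

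**5. Scale.** Samples of 150 to 160 have 77–80% power for a correlation of 0.22 and 90–91% for 0.26. At r = .4 to .5 the spurious b (0.16 to 0.25) is therefore of the same order as a B path this sample can detect, and the output alone would not tell the two apart.

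**6. How far adjustment goes.** It helps only as far as the T1 measures capture the trait. With a baseline measure of reliability 0.8, a separate simulation (a = 0.91) gives 4%, 6%, 7% and 12% at r = .2 to .5. Reliability 0.5 gives the fourth row above. T1 ECBI alone, if correlated only .2 with the trait (assumed), leaves 7%, 19%, 51% and 88%.

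**The case against.** **The plan may well adjust.** The mediation section is a short summary that refers to published criteria, Mplus code and a figure that is not shown, and a separate analysis plan may list covariates. A reader might infer that the plan commits to an unadjusted model. The text does not support that; it is silent. What stands is that the model as described names three variables and reads the second path causally, while the only covariate rule in the article belongs to another hypothesis and answers a different question.

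**The wording is that of a hypothesis.** The article speaks of a potential mediator and of testing whether a path exists, and it promises no proof. That is fair, but a test that cannot separate the causal path from a common cause does not test what the sentence says.

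**The size is assumed.** Correct. At r = .2 the excess is small, and the high rates need a single trait correlated .4 or more with both variables. A reader might infer that a false mediation finding is likely; nothing in the article says which r applies.

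**The adaptation step.** A reader might cite the step in DPT-TP where "parents will be asked to report about the current state at home, and this will be used to recommend whether to complete" certain modules as a built-in baseline confounder. It is not one. The report comes at the end of the first module, after randomisation, and is described only for DPT-TP. It bears on the denominator of the completion rate, which is a separate matter that T1 covariates need not address.

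**Covariates are no cure, and a long list is costly.** Both points stand. Two candidate scales have reported alphas of only 0.75 (MaaP) and 0.72 to 0.77 (APQ), and the SPP is new with none given. The demographic questionnaire's contents are not listed, so education or single parenthood cannot be assumed to be available.

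**Conclusion.** The concern holds in a limited form. As described, the Hypothesis 3 model leaves the between-parent completion-to-outcome path open to confounding by stable parent characteristics, and neither a lag nor a time term closes it. With 160 families, a large A path and no true completion effect, false mediation runs at about 7% for an assumed trait correlation of .2, about 20% at .3 and about 50% at .4. These rates rest on an assumed single confounder acting equally in both arms and on simplified versions of the planned model; the direction of the problem does not depend on them.

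The documents do not show that the final analysis will be unadjusted, that the confounding is strong, or that baseline adjustment would remove it. The Hypothesis 1 and 2 comparisons and the total arm effect are unaffected. This is a cheap improvement worth making to one of the three aims, not a flaw in the trial's main comparison.

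**What to change.** In the Mediation Analyses section:

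1. Pre-specify a short set of T1 variables as level-2 covariates in both the completion and the outcome equation: T1 score of the outcome, T1 ECBI Intensity, one T1 self-efficacy score, one T1 parenting-practice score, and child gender. The scales are already administered at T1, and child gender is known because it stratifies the randomisation.
2. Add one sensitivity analysis showing what residual completion-outcome correlation would bring the indirect effect to zero. In the working above, a spurious b of 0.16 corresponds to a residual correlation of 0.4 × 0.4 = 0.16.
3. State that the completion-to-outcome path is not randomised, and report a positive result as consistent with mediation under an assumption of no unmeasured confounding.

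**Cost.** No new data or visits. About five extra parameters per equation, so about 5 × 2 = 10 per outcome on 160 families, and fewer where the outcome is itself one of the listed scores. The indirect effect may come out smaller, and the bias is only partly removed because T1 measures capture the trait imperfectly. Table 1 starts analysis in January 2027, so the change can be fixed beforehand.

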**Figure 2 figure2:**
[figure not shown]
A 2-1-1 mediation model. DPT-STD: standard digital parent training program; DPT-TP: digital parent training program enhanced based on therapeutic persuasiveness quality; TP: therapeutic persuasiveness.

#### Power Estimation

Data emerging from the pilot suggest a large effect size difference in module completion rates and medium effect size differences between the 2 intervention groups in terms of change in ECBI scores and parenting variables post intervention (eg, primary hypothesis Cohen *d*s=0.43; 0.54) [39]. Taking the smaller effect size as an approximation (Cohen *d*=0.43), a total sample size of 80 participants in each of the 2 conditions and a total of 160 participants will provide 0.85 power (α=.05, 1-tailed) to detect significant differences in the primary outcomes (intent-to-treat analysis).

For our mediation analyses, we assume a large effect size difference in program completion rate based on TP quality (the A path), and a small to moderate effect size (correlation) between program completion and change in child behavior problems (the B path). Therefore, a sample size of 160 participants in total is higher than 150 participants, which would be sufficient to examine the relationship between program completion rate (the mediating variable) and child behavior problems (the predicted variable; for a review of sample size estimations for mediation effects, see [69]).

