#### Recruitment Procedure

Parents will be recruited through relevant social media parenting groups, Facebook advertisements, and pamphlets sent to relevant childcare settings. Prospective participants will be directed to the project website, which will offer basic information and a link to a brief eligibility screener consisting of the exclusion criteria and 9 items assessing the parents’ experience of their child’s behavior, based on *Diagnostic and Statistical Manual of Mental Disorders, Fifth Edition* criteria for oppositional defiant disorder (to pass screening parents had to receive an average of 4.22 or above). Screening, interest, and parents’ understanding of the terms of the study will be confirmed by a phone call with a research assistant. Parents will then be directed to a web-based informed consent form, followed by the baseline assessment battery. Once participants have completed baseline assessments and are deemed eligible, they will be randomly assigned to one of the 2 conditions (1:1), stratified for child gender, by an independent researcher who is blind to their assessments and has exclusive access to the assignment sequence. A computer-generated randomization procedure will be used with randomly generated block sizes of 2, 4, and 6. Ineligible participants will be informed about available public mental health care services.

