### Analytic Plan

#### Preprocessing Steps: Data Audit and Missing Data

The final trial dataset will be accessed by the research coordinators, a statistician, and the principal investigator. Preprocessing will include an examination of data accuracy to identify and correct errors and to ensure that all data are in range. In addition, univariate outliers will be identified (observations that are 3 SDs from the mean in both directions) and will be corrected using winsorizing [64]. Normality (ie, skewness and kurtosis) will be examined for all variables using standard tests (Shapiro-Wilk test and Kolmogorov-Smirnov test). If data significantly differ from a normal distribution according to these tests, we will use transformations depending on the precise deviations from normality (eg, positive skewness, negative kurtosis). Possible transformations will include square root, natural log, inverse, and the Box-Cox transformation [65]. The pattern of missing data will be assessed using Little’s Missing Completely at Random test. Data that are missing completely at random or missing at random will be imputed using multiple imputations with 5 datasets. All preprocessing will be done using SPSS software (IBM Corp).

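### The stated 0.85 power is right for a 1-tailed test, but the efficacy analysis as planned is a non-directional ANOVA F-test, for which power at d=0.43 is about 0.77 with complete data

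*Protocol article*

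**What the plan says.** The Power Estimation section of the protocol article starts from two pilot effect sizes, 0.43 and 0.54, and plans on the lower one: "Taking the smaller effect size as an approximation (Cohen *d*=0.43"). With "a total sample size of 80 participants in each of the 2 conditions and a total of 160 participants", it states that the trial "will provide 0.85 power (α=.05, 1-tailed) to detect significant differences in the primary outcomes (intent-to-treat analysis").

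The section on Hypotheses 1-2 gives the efficacy analysis: "Hypothesis 2 will be examined using two 2-way ANOVAs with treatment type (DPT-STD vs DPT-TP), measurement" (pre vs post in one model, pre vs follow-up in the other) and their interaction. If assumptions fail, it falls back on weighted least squares, Welch or Brown-Forsythe. It mentions no one-sided contrast, one-sided rejection rule or halved p-value.

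The hypothesis itself is directional: "parents who receive DPT-TP will report greater improvements in child behavior problems" than parents given the standard program. Missing data are foreseen in the preprocessing section: "Data that are missing completely at random or missing at random will be imputed using multiple imputations with 5 datasets". The abstract gives the recruitment target as 160 families, the same number that enters the power calculation.

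**The concern.** The power was computed for one test and a different one is planned. With two arms and two time points, the interaction F-test is the square of the two-sample t-test on change scores. Squaring removes the sign, so the test at .05 is equivalent to a two-sided t-test at .05. A directional hypothesis does not alter that; only a directional rejection rule would.

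The article describes the trial as fully powered, and for the efficacy hypothesis that description rests on this one figure. If the analysis is run as written, a null result on child behavior problems would be read as stronger evidence against a d=0.43 effect than the design supports. If instead the results are reported one-sided, that choice would not be anchored in the analysis section and could look as though it was made after the data were seen.

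A second, smaller matter is that all 160 recruited families are counted as contributing full outcome information, although the plan expects some data to be missing.

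**Working it through.** **Inputs.** d=0.43, n=80 per arm, alpha .05, 1-tailed (Power Estimation); 1:1 allocation (Recruitment Procedure); arm-by-measurement interaction with two levels of each factor (Hypotheses 1-2 Analytic Plan). As in the plan's own calculation, d is read as the standardised between-arm difference in change.

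**Formula.** Power comes from the noncentral t distribution with df = 2n − 2 and noncentrality d × √(n/2).

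For n=80: df = 158 and noncentrality = 0.43 × √40 = 2.72.

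**Step 1: the plan's own figure.** The one-sided critical value is t = 1.655. Power = P(T > 1.655) = **0.856**. The stated 0.85 is reproduced.

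**Step 2: the planned test.** The two-sided critical value is t = 1.975. Power = P(|T| > 1.975) = **0.771**. As a cross-check through the F-test itself: F(1, 158) with noncentrality 160 × (0.43/2)² = 7.396, which is 2.72², and critical value 3.90 = 1.975², also gives 0.771.

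The type II risk is 1 − 0.771 = 0.229, about 23%, against 1 − 0.85 = 15% as stated.

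**Step 3: scale.** Two-sided power of 0.80 at d=0.43 needs 86 complete cases per arm (85 by the normal approximation), and 0.85 needs 99 (98). These show the size of the gap only. At the larger pilot effect, d=0.54, two-sided power with 80 per arm is 0.92.

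**Step 4: missing outcomes, illustration only.** The documents give no dropout rate, so the rates below are assumed. Loss is treated as complete-case loss, equal in both arms.

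| Assumed loss | n per arm | One-sided power | Two-sided power |
|---|---|---|---|
| 0% | 80 | 0.856 | 0.771 |
| 10% | 72 | 0.822 | 0.727 |
| 20% | 64 | 0.781 | 0.675 |
| 30% | 56 | 0.731 | 0.616 |

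One-sided power is still 0.852 with 79 per arm, so the stated figure tolerates about one loss per arm.

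**The case against.** The strongest reply is that nothing was hidden or miscalculated. The inputs are all declared, including the sidedness, and 0.85 follows from them. This stands, and it rules out one tempting reading: that the power figure is an arithmetic error. It is not.

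It may also be said that the plan does mention a 1-tailed test, since Power Estimation is a subsection of the Analytic Plan, and that this is the only statement of sidedness in the article. This is true, so a reader should not infer that one-sided testing appears nowhere in the plan. What is missing is any one-sided rule where the efficacy test is specified. Because the interaction has 1 df, a directional version is available from the same model, and prespecifying it would give back 0.856 with complete data. So two reconciliations are possible, and the documents do not show which one the investigators intend.

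Could the matter be left to a statistical analysis plan that is not shown? The fine detail of testing could. But this article states both the power basis and the test, and as they stand the two do not agree.

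On attrition, a reader might infer that the trial will fall to 0.68 or 0.62. The documents do not support that: the rates are assumed, the T2 and T3 measurements may let multiple imputation recover part of the loss, and program non-completion in the pilot is not the same as a missing assessment. Imputation keeps every family in the analysis but does not generally restore all the information in a missing final outcome, so leaving out any allowance remains worth a sentence.

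Finally, 0.43 is the lower of the two pilot effects. That is fair context, but it is the effect the plan itself chose as its basis.

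**Conclusion.** The point holds as a mismatch between two sections. The stated 0.85 applies to a 1-tailed test; the ANOVA interaction F-test at .05, as written, has power of about 0.77 for d=0.43 with 80 analysed per arm. The difference is 0.856 − 0.771, or about 8.5 percentage points. This rests on reading d as the standardised difference in change and on the F-test being used with its ordinary non-directional p-value at .05.

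The missing-data part is secondary. No allowance was made, but its size cannot be fixed from the documents; 0.73, 0.68 and 0.62 at 10%, 20% and 30% loss are illustrative values.

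It does not follow that the sample size must change, or that type I error or the effect estimates are affected. What needs correcting is the power claim, or the test specification, so that the two agree.

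**What to change.** Keep N=160. In Power Estimation, remove the 1-tailed qualifier and restate the power for the planned test, for example: with two-sided alpha .05 and d=0.43, power is 0.77 with complete data; for illustration, about 0.73, 0.68 and 0.62 if 10%, 20% or 30% of outcomes were missing, on a complete-case basis and before any recovery through multiple imputation.

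Alternatively, if a directional test is truly intended, write the one-sided contrast and its alpha into the Hypothesis 2 plan before analysis. The 0.85 can then stay for complete data. The article schedules analysis from January 2027.

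If the investigators wish to quote a higher figure from a baseline-adjusted model, it should be given separately, because that is a different analysis from the planned ANOVA and depends on a pre-post correlation r that the article does not state. With d in change-score SD units, the adjusted effect is d × √(2/(1+r)). Two-sided power with 80 per arm would then be about 0.87 at r=0.55, 0.81 at r=0.80 and 0.79 at r=0.90.

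The cost is a rewritten sentence or two and, if the two-sided test is kept, a less favourable stated figure. No extra participants are needed.

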### Pilot Study

A pilot study was recently conducted to initially examine the causal impact of therapeutic persuasiveness on user adherence to the program and the program’s efficacy. In this pilot, parents of children with behavior problems were randomly allocated to receive either a standard DPT (DPT-STD) or a DPT designed with enhanced quality of therapeutic persuasiveness (DPT-TP). Both interventions used the same evidence-based content but differed in the quality of their therapeutic persuasiveness. Parents from 88 families who have a child with behavior problems were enrolled in the study. Compared with DPT-STD (n=43), participants allocated to DPT-TP (n=45) used the program significantly more (*P*s<.001; Cohen *d*s=0.91-2.22). In terms of program completion, 68.9% (31/45) of DPT-TP participants completed it compared with 27.9% (12/43) of DPT-STD participants. Significant differences between the interventions were also found in reported improvements in child behavior problems, favoring DPT-TP (*P*s<.05; Cohen *d*s=0.43-0.54) [39].

In a qualitative thematic analysis of semistructured interviews, DPT-TP users identified features embedded exclusively in the enhanced program, such as call-to-action reminders and assessment-based feedback, as important components that helped them in their process of change [40].

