#### The Parenting Scale

Parental disciplinary behaviors in response to their child’s misbehaviors will be assessed using 2 PS subscale scores, Over-reactivity (11 items) and Laxness (10 items), which reflect effective discipline and discipline mistakes on either end, using a 7-point Likert scale. Internal consistency scores (Cronbach α) have been reported (Laxness α=0.83; Over-reactivity α=0.82). These scores have also been found to correlate significantly with observational measures of dysfunctional discipline and child misbehavior [47].

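### The 0.85 power is claimed for unnamed, plural primary outcomes but holds only for one outcome at one time point, while Hypothesis 2 has 14 tests of equal rank

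*Protocol article*

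**What the plan says.** The hypotheses under This Study predict greater improvement with DPT-TP in child behavior, parenting practices and parental self-efficacy, "as measured pre-post and pre-follow-up". The Hypotheses 1-2 Analytic Plan repeats the list without ranking it: "Child behavior problems (ECBI Intensity), parenting practices (SPP, PS scales, and APQ), and parental self-efficacy (PTC and MaaP) will be the dependent variables". The Parenting Scale contributes two scores ("2 PS subscale scores, Over-reactivity (11 items) and Laxness (10 items"), so there are seven. Each goes into two ANOVAs, with "measurement (pre vs post in the first ANOVA and pre vs follow-up in the second". That section gives no significance level.

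The only alpha in the article is in Power Estimation, where 80 per arm "will provide 0.85 power (α=.05, 1-tailed") "to detect significant differences in the primary outcomes". The calculation uses one effect size: "Taking the smaller effect size as an approximation (Cohen *d*=0.43").

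The article's hints about what is primary do not agree:
- Power Estimation speaks of ECBI change and parenting variables together, then attaches the label of primary hypothesis to d values of 0.43 and 0.54.
- The Pilot Study section reports that same range for one domain only: "Significant differences between the interventions were also found in reported improvements in child behavior problems, favoring DPT-TP".
- The Discussion puts program usage first among the expected principal findings.

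**The concern.** A power figure describes a defined test or a defined success rule. Here it is attached to a plural that is never spelled out, next to an efficacy hypothesis with 14 unranked tests. Two things are at stake. First, a reader cannot tell which result the 0.85 protects. Second, nothing in the article prevents support for Hypothesis 2 from resting on whichever scale or time point succeeds. That matters because This Study presents the trial as fully powered and able to support the hypotheses strongly.

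**Working it through.** **Inputs from the article.** 80 per arm, 1:1 allocation, d=0.43, alpha .05 one-tailed, seven scores, two contrasts. With two time points, the treatment-by-time interaction is equivalent to a two-sample comparison of change scores. I take d as standardized on change and assume no loss of information from dropout. The pilot effects are postintervention, and no effect size is given for follow-up.

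**Number of tests.** ECBI Intensity, SPP, PS Over-reactivity, PS Laxness, APQ, PTC and MaaP make 7 scores; 7 × 2 = 14 tests.

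**Reproducing the 0.85.** The noncentrality is δ = d × √(n/2) = 0.43 × √40 = 2.72.
- One-sided .05, normal: Φ(2.720 − 1.645) = 0.859; noncentral t on 158 df: 0.856. This matches the stated figure.
- Two-sided .05, normal: Φ(2.720 − 1.960) = 0.776; noncentral t: 0.771. This does not match.

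So the 0.85 is the power of one one-tailed comparison.

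**Readings of the plural.** The article gives no correlations between the test statistics, so a common correlation ρ is assumed and varied.

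All seven postintervention scores significant, one-sided .05, d=0.43 on every scale: power = ∫ φ(u) [Φ((δ − 1.645 + √ρ u)/√(1 − ρ))]^7 du. At ρ=0 this is 0.859^7 = 0.344.

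Any of 14 tests significant in favor of DPT-TP when no effect exists: 1 − ∫ φ(u) [Φ((c − √ρ u)/√(1 − ρ))]^14 du. Here c=1.645 for one-sided .05 tests, and c=1.960 for two-sided .05 tests counted only in that direction. At ρ=0 these are 1 − 0.95^14 = 0.512 and 1 − 0.975^14 = 0.298.

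| ρ (assumed) | Power, all 7 at T4 | False positive, any of 14, one-sided | False positive, any of 14, two-sided, favoring DPT-TP |
|---|---|---|---|
| 0 | 0.34 | 51% | 30% |
| 0.3 | 0.48 | 37% | 22% |
| 0.5 | 0.56 | 29% | 17% |
| 0.7 | 0.65 | 21% | 12% |
| 0.8 | 0.69 | 17% | 10% |

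As a sensitivity check, the correlation between two tests that differ in both scale and time point was set to the product of the between-scale and between-time correlations. Over 0.3 to 0.8 the ranges become 41% down to 19% one-sided, and 24% down to 11% two-sided in favor of DPT-TP.

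Bonferroni sharing of alpha, one-sided, noncentral t: power per outcome is 0.60 at .05/7 and 0.50 at .05/14.

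At least one of the seven significant: power is 0.96 or higher, but this is the rule that inflates error.

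None of these set-wise readings yields 0.85.

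**The case against.** The case on the other side is substantial.

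- **The article is condensed.** It cites a registration and a numbered full protocol, neither shown here. An outcome ranking or a multiplicity rule may be there, so the absence of an adjustment is not itself a fault. This stands.
- **The .05 per test is inferred.** The analytic plan sets no level; the only alpha is in the sample-size sentence. This stands, and the error figures above are conditional on it.
- **No any-one-of-14 rule is stated.** Hypothesis 2 is worded conjunctively, and if every score had to succeed there would be no inflation of this kind. This stands. Inflated error and lost power arise under different rules and cannot both be charged at once. But the article states neither rule, and 0.85 fits neither.
- **Power per outcome at the smaller pilot effect is conventional, and the arithmetic is right.** This also stands. The defect is what the number is attached to.

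A reader might infer that a false-positive claim of success is more likely than not. That needs 14 independent one-sided tests, or counting two-sided rejections in favor of either arm. Independence is not credible, because the same parent reports every scale and both contrasts share one baseline.

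What the objection does not repair is the sentence itself. If an unseen document adjusts alpha, 0.85 at .05 does not describe the adjusted tests. If it names one primary outcome, the plural is wrong.

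**Conclusion.** The point holds in limited form. The article gives the power of a single comparison to a set of primary outcomes that it does not identify, and it ranks none of the 14 efficacy tests. For one outcome at one contrast the 0.85 is sound on one-tailed terms. As a requirement on all seven postintervention scores it would be about 0.34 to 0.69. If any of the 14 tests could carry the claim, the risk of a false finding for DPT-TP would be about two to seven times the nominal 5%: 10% to 22% two-sided, 17% to 37% one-sided.

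These sizes rest on assumed correlations, on d=0.43 for scales where the Pilot Study section reports no such effect, and on .05 for each test. It would go too far to say that the power calculation is wrong, that the plan adopts an any-success rule, or that multiplicity is left uncontrolled in the full protocol. The documents show none of these.

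**What to change.** Name one primary efficacy outcome and time point. If the registration or full protocol already names one, use it. Otherwise ECBI Intensity from T1 to T4 is the natural choice: it is the eligibility measure, and it matches the domain and timing of the pilot effect behind the calculation. Label the other 13 efficacy tests secondary. Either state a multiplicity adjustment for them or report them as supportive, without confirmatory claims; which of the two is a matter of judgment. Change the power sentence to refer to the primary outcome in the singular.

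Also make the sidedness agree. Either state that the primary comparison is one-tailed at .05, as powered, or keep the ordinary two-sided interaction test and report 0.77. On the normal approximation, 0.85 two-sided would need 98 per arm.

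The change is to wording, needs no new data, and can be made before analysis starts in January 2027. The price is weaker confirmatory claims for the secondary scales. Keeping the outcomes co-equal costs more: with Bonferroni, one-sided, 0.85 power per test would need 132 per arm for 7 tests or 151 for 14.
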